**Figure 1 figure1:**
[figure not shown]
Study design diagram. dMH: digital mental health; GAD-7: Generalized Anxiety Disorder–7; PHQ-9: Patient Health Questionnaire–9.

### Participant Recruitment

#### Eligibility

Participants will be recruited from the Australian community and will be eligible for the trial if they meet the following criteria: aged ≥18 years, are Australian residents, have access to the internet, able to register their interest via the web using an email address, able to read and write in English, and have symptoms or a diagnosis of anxiety or depression (as assessed by the Mini International Neuropsychiatric Interview [MINI] 7.0.2 [13]).

Participants will be excluded if they are currently receiving psychological treatment for their mental health, have moderate to severe levels of alcohol or substance use, have active psychosis or active suicidal intent or plan, have unstable bipolar disorder (as assessed by MINI 7.0.2 [13]), or take unstable doses of medication (ie, eligible participants will need to be on the same doses of their prescribed medications for at least one month before commencing the intervention).

#### Screening Procedures

Potential participants will register their interest to participate in the study via the completion of a screening contact form on the study’s website. Interested participants will be presented with the Plain Language Information Statement before completing the contact form. Consent will be obtained at 2 intervals (upon initial completion of the contact form and again when entered into the trial), whereby participants will be required to click a button, *I agree*, indicating that they consent to the study. After consent is obtained, participants will be invited to participate in a brief telephone screening interview that corresponds with the *Diagnostic and Statistical Manual for Mental Disorders, Fifth Edition* (DSM-5) [14] criteria for generalized anxiety disorder, social phobia, panic disorder, agoraphobia, and major depressive disorder. During the telephone interview, the participants’ ability to attend a video chat assessment will be determined. The interview will conclude with exploration of their motivation to improve their symptoms of anxiety or depression.

Eligible participants will be scheduled for a diagnostic assessment. That is, administration of MINI 7.0.2 [13] via video chat technology accessed through the My Digital Health platform of Federation University. This clinical assessment will determine the presence of mental health symptoms (allowing for assessment of the inclusion and exclusion criteria of the study) and assignment of clinical severity ratings for any identified disorders. MINI is a short, structured interviewing tool designed to aid DSM-5 diagnosis and monitor the clinical outcomes of the 17 most common mental disorders. It has a mean administration time of 15 minutes, with questions requiring a “yes” or “no” response (eg, “In the past two weeks, were you much less interested in most things or much less able to enjoy the things you used to enjoy, most of the time?”). MINI has been validated against the long Structured Clinical Interview for Diagnostic and Statistical Manual for Mental Disorders diagnoses and has been identified as a more time-efficient diagnostic tool, demonstrating excellent interrater reliability (*k*=0.88-1) [13]. MINI will be administered before the intervention (week 0); after the intervention (week 9); and 3 months after the treatment, at follow-up (week 21).

### Participant Measures

#### Overview

Eligible participants will be given access to the preintervention (week 0) self-report questionnaire assessment comprising a demographic questionnaire (including age, sex, relationship status, education level, alcohol and other drug use, medication use, and current and past access to mental health services). Participants will also be asked to complete a short questionnaire package at weeks 3 and 6 and outcome measures after the intervention (week 9) and at the 3-month follow-up (week 21). At week 3, participants’ questionnaire data for anxiety (GAD-7) and depression (PHQ-9) will be compared against the preintervention outcome data to assess whether the stepped care rules of the trial have been met and whether a therapist is required to be assigned to a participant. Table 1 shows the schedule and frequency of the assessments during the trial for participants.

**Table 1 table1:** Schedule of enrollment and assessments.

Concepts and measures			Preintervention period (week 0)		Midintervention period (weeks 3 and 6)		Postintervention period (week 9)		Follow-up period (week 21)
**Screening**									
	Anxiety and depression screen (DSM-5^a^)	✓							
	Diagnosis (MINI^b^ 7.0.2)	✓				✓		✓	
**Primary outcomes**									
	Anxiety (GAD-7^c^)	✓		✓		✓		✓	
	Depression (PHQ-9^d^)	✓		✓		✓		✓	
**Secondary outcomes**									
	Working alliance (WAI-S^e^)			✓		✓			
	Health status (AQol^f^)	✓				✓		✓	
	Health resources			✓		✓			
**Moderators**									
	Motivation (CMOTS^g^)	✓				✓			
	Self-efficacy (BPSES^h^)	✓				✓			
	Demographic questionnaire	✓				✓		✓	
**Treatment**									
	System Usability Scale			✓					
	Preferences questionnaire	✓							
	Satisfaction questionnaire					✓			
	Semistructured feedback interviews			✓		✓			

^a^DSM-5: *Diagnostic and Statistical Manual for Mental Disorders, Fifth Edition*.

^b^MINI: Mini International Neuropsychiatric Interview.

^c^GAD-7: Generalized Anxiety Disorder–7.

^d^PHQ-9: Patient Health Questionnaire–9.

^e^WAI-S: Working Alliance Inventory–Short.

^f^AQol: Assessment of Quality of Life.

^g^CMOTS: Client Motivation for Therapy Scale.

^h^BPSES: Bipolar Self-efficacy Scale.

#### Anxiety

The GAD-7 [15] is a self-report measure that assesses anxiety symptoms over the past 2-week period. Total scores range from 0 to 21, with high scores suggestive of more severe anxiety symptoms. Each item is rated on a 4-point scale, with scores >8 indicative of clinically significant anxiety symptoms, warranting further evaluation. Scores of 5, 10, and 15 represent the cutoff points for mild, moderate, and severe anxiety symptoms, respectively. The GAD-7 is sensitive to changes in generalized anxiety disorder, social phobia, panic disorder, and posttraumatic stress disorder, with a score of >5 points indicative of clinically meaningful change over time [15]. The GAD-7 has strong psychometric properties [15].

#### Depression

The PHQ-9 [16] is a self-report measure designed to assess symptoms of major depressive disorder over the past 2-week period. Total scores range from 0 to 27, with high scores indicative of great depressive symptoms. Each item is rated on a 4-point scale, with scores >10 used as cutoff to indicate the presence of clinically significant depressive symptoms. Scores of 5, 10, 15, and 20 represent the cutoff points for mild, moderate, moderately severe, and severe depressive symptoms, respectively. The PHQ-9 has strong psychometric properties [16].

#### Working Alliance

The Working Alliance Inventory–Short (WAI-S) [17] is an abbreviated version of the Working Alliance Inventory based on the theory by Bordin [18] and comprises the following subscales: goal agreement, task agreement, and bond. In this study, the WAI-S is available in a therapist version (10-item scale) and a participant version (12-item scale), with both versions to be used to capture the strength of the therapeutic alliance from both perspectives. Total scores range from 12 to 60, with high scores suggestive of strong therapeutic alliance. Each item is rated on a 5-point scale, and the measure has strong psychometric properties [17]. To assess participants’ technological alliance with the self-help dMH program, the wording of the items of the WAI-S have been slightly modified for this study, to capture participant ratings for a dMH program without therapist assistance.

#### Health Status

The Assessment of Quality of Life (AQol) [19] is a 12-item, self-report measure designed to assess ratings of health-related quality of life in a variety of life areas such as independent living, illness, social relationships, psychological well-being, and physical senses. The AQol can be scored in 2 ways—as a psychometric measure and as a utility measure. As a psychometric measure, scores are used to derive a simple psychometric score for health-related quality of life and provide profile scores on each of the 5 dimensions. When the AQol is scored as a utility measure, it can provide dimension scores and an overall index of the health state, which can be used in economic evaluation and cost analysis. The AQol has been validated across several countries, has been shown to have high degree of internal consistency (Cronbach α=.81), and is deemed an acceptable measure of health-related quality of life.

#### Health Resources

A Health Care Resource Usage questionnaire for cost-effectiveness has been specifically designed for the study to evaluate participants’ primary and secondary health care consultations and admissions, use of antidepressant and antianxiolytic medication, and resource use associated with treatment received in the trial. The treatment received in the trial will encompass the amount of therapist time required, supervisor’s time, internet access, and computer use.

#### Motivation

The Client Motivation for Therapy Scale (CMOTS) [20] is a self-report measure designed to assess the degree to which an individual is motivated for therapy and the impact of a person’s motivation on treatment effectiveness and mental health symptoms. The 24 items assess 6 dimensions of the self-determination continuum of motivation proposed by Deci and Ryan [21]: intrinsic motivation, 4 forms of extrinsic motivation (integration, identification, introjection, and external regulation), and amotivation for therapy. The CMOTS obtains subscale scores for each type of motivation, with high scores reflecting high levels of each type of motivation. Each item is rated on a 7-point scale. The CMOTS has strong psychometric properties [20].

#### Self-efficacy

The Bipolar Self-efficacy Scale (BPSES)–Modified [22] has been slightly modified for use in this study to measure the self-efficacy of participants with anxiety and depressive symptoms opposed to bipolar disorder symptoms. The 17 items of the modified self-report measure of self-efficacy assess how confident an individual feels in performing a range of activities related to their mental health such as taking their medication as prescribed, maintaining regular hours of sleep, and identifying early warning signs of anxiety and depression (as opposed to bipolar symptoms). Each item is rated on a 10-point scale, with high scores indicative of high levels of self-efficacy. The BPSES has strong psychometric properties, with sensitivity to detect change over the course of treatment [22].

#### Usability

The System Usability Scale [23] is a 10-item measure designed to assess participant perceptions of the usability of a program. The System Usability Scale will be used in this study to assess participants’ ease and perceptions about the dMH program’s usability (eg, “I thought the program was easy to use”). Each item is rated on a 5-point scale, with high scores reflective of increased system usability.

#### Preferences

A bespoke preferences questionnaire has been purposively developed to assess participants’ preferences for treatment before commencing the trial. Participants are presented with brief information about each of the 3 treatment conditions (dMH program only, low intensity therapist assistance, and high intensity therapist assistance), which they are then asked to rank in order of their preference.

#### Satisfaction

A purposively designed 10-item satisfaction questionnaire has also been developed to assess participants’ level of satisfaction with the treatment received. Overall, 8 of the 10 items are rated on a 4-point scale. For the other 2 questions, participants are asked to qualitatively share what they believe were the best and worst parts of the dMH treatment program.

### Primary Outcomes

The primary outcomes will be participants’ level of anxiety (GAD-7 [15]) and depression (PHQ-9 [16]).

### Secondary Outcomes

The secondary outcomes being assessed are working alliance (WAI-S [17]), health status (AQol [19]), health resources, self-efficacy (BPSES [22]), and motivation (CMOTS [20]).

### Treatment Conditions

#### Life Flex Program

The primary dMH intervention in each of the 3 treatment conditions is Life Flex, which is one of the dMH programs housed and offered via the My Digital Health platform. Life Flex is a third-wave transdiagnostic biopsychosocial treatment approach that aims to increase psychological flexibility, through cognitive behavior therapy, emotion regulation, and positive psychology principles, for anxiety and depression. The Life Flex program is suitable for individuals with or those without a DSM-5 diagnosis of anxiety or depression.

Life Flex teaches participants biopsychosocial *life skills*. It comprises 6 core modules, along with an introductory module and a booster module. The introductory module provides a rationale for the program, discusses brain plasticity and change processes, includes information about anxiety and depression, and explores factors contributing to motivation for change. Each of the 6 core modules focuses on increasing flexibility within a particular domain, such as biological (eg, breathing, nutrition, and sleep), emotional (eg, increasing emotional awareness), thinking (eg, identifying and challenging unhelpful cognitions), behavioral (eg, increasing pleasurable activities), wellness (eg, loving kindness), and life flexibility (eg, consolidating the life skills learned and goal setting). The booster session focuses on consolidation and reinforcement of learning. Further information about the Life Flex program can be accessed via a forthcoming paper that has recently been accepted for publication in JMIR Formative Research [24].

Each module of the Life Flex program will take approximately 25 minutes to complete. In addition, to reinforce the module-based information, there are 20 to 30 minutes of offline activities each week. Offline activities include applying the concepts and techniques discussed in the modules (eg, self-monitoring depressive and anxiety symptoms), undertaking one of the biological and wellness flexibility intervention strategies, monitoring emotions and thoughts, and undertaking the gradual exposure or behavioral activation activity. Participants will also receive automated emails (eg, to remind them to log in or to complete the questionnaires) and will be asked several questions at the beginning of each module to help gauge their progress. Module features include text, graphics, audio, video, editable forms, interactive games (eg, brain training), and downloads. Modules can be accessed via web, mobile phones, or tablet devices.

#### Life Flex Program–Only Condition

The treatment in step 1 of the trial will comprise the *program-only* Life Flex treatment program, whereby participants complete the fully automated, self-help program without therapist assistance. If participants do not improve in the *program-only* condition within the first 3 weeks (ie, no change in anxiety or depression symptoms, symptoms remain in the severe range, or noncompletion of the preintervention or week 3 questionnaire) or do not engage with the program (ie, noncompletion of the introduction module or module 1), they will be randomized to augment their program with either *low* therapist assistance (ie, one 10-minute support session per week) or *high* therapist assistance (ie, one 50-minute therapy session per week), delivered via video chat technology by provisionally or generally registered psychologists. Participants who improve or engage with the Life Flex program (program only) within the first 3 weeks maintain their no therapist assistance program. Participants who remain in the *program-only* treatment condition will complete the Life Flex program on a scheduled release design, with a new module being released every week, with the exception of module 4 (participants are given 2 weeks to work through and practice module-4 content).

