### Objectives

The purpose of this study is to present a protocol designed to evaluate various support intensities of a dMH treatment program for anxiety and depression within a mixed methods design. Therefore, the study has the following primary objectives:

To compare the efficacy of clinical outcomes (anxiety [Generalized Anxiety Disorder–7; GAD-7] and depression [Patient Health Questionnaire–9; PHQ-9] symptoms) among the 3 treatment conditions (dMH program only, low-intensity therapist assistance, and high-intensity therapist assistance), with particular focus on whether therapist-assisted support produces greater reductions in anxiety and depression severity compared with those produced by dMH program–only support.To examine the role of motivation and self-efficacy on engagement, adherence, and clinical outcomes (anxiety [GAD-7] and depression [PHQ-9] symptoms) among the 3 treatment conditions (dMH program only, low-intensity therapist assistance, and high-intensity therapist assistance) at postintervention (week 9) and follow-up (week 21) assessments, compared with those at preintervention (week 0) assessment.To explore participant and therapist experiences and satisfaction with assessment and therapist assistance delivered via video chat technology, using semistructured interviews; specific areas of focus will include the ability to develop and maintain therapeutic relationships, implementation barriers and facilitators, and identified strengths and limitations of video chat technology for conducting assessments and delivering dMH treatment.To explore therapist training and implementation experiences in the delivery of dMH interventions.To use a mixed methods analysis to examine factors affecting participant attrition in each of the treatment intensities; quantitative examination of preferences, treatment condition allocation (dMH program only, low-intensity therapist assistance, and high-intensity therapist assistance), and attrition rates will be explored; qualitative exploration of participant reasons for withdrawal and nonengagement with therapist support will also be conducted using semistructured interviews.To explore the outcomes of working alliance, health resources, and health status among the 3 treatment conditions (dMH program only, low-intensity therapist assistance, and high-intensity therapist assistance).

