## Methods

### Trial Design

This trial will follow the International CONSORT (Consolidated Standards of Reporting Trials) guidelines and evaluate the conditions using an adaptive randomized clinical trial design [12]. The clinical trial also adheres to SPIRIT (Standard Protocol Items: Recommendations for Interventional Trials; Multimedia Appendix 1). All information will be strictly confidential, yet subject to legal limitations (eg, legal subpoena), and only accessed by the investigators. Data are stored securely using 256-bit encryption Secure Sockets Layer and Transport Layer Security software when information is transmitted. Any hard copy data will be stored securely in lockable filing cabinets at the Federation Community Psychology Services at Federation University.

Eligible participants will be given access to a self-help dMH treatment program (Life Flex) and have their symptoms of anxiety or depression evaluated at day 15 to assess whether they meet the criteria to have their treatment program augmented with therapist assistance. Participants will be considered as eligible to be *stepped up* to a therapist-assisted condition if they meet any of the following criteria: they have not read the introduction module or module 1 of the Life Flex program; have symptoms of anxiety or depression that have deteriorated by >5 points (as assessed by comparison of their baseline depression [PHQ-9] and anxiety [GAD-7] scores against their week-3 scores); show symptom improvement, but their scores remain in a severe range; and are yet to complete the week-3 questionnaire assessment.

Outcomes will be assessed before the intervention (week 0), during the intervention (weeks 3 and 6), after the intervention (week 9), and at the 3-month follow-up (week 21). Results will be disseminated via publication. Figure 1 illustrates the study’s design and expected participant flowchart.

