### Randomization

The process of randomly allocating participants to either the low-intensity or high-intensity treatment groups will comply with CONSORT guidelines. A block randomization design will be used to randomly allocate each participant to either the low-intensity or high-intensity therapist assistance condition throughout the trial. Random allocation will occur when a participant has met the criteria to be *stepped up* to have their Life Flex program augmented with therapist assistance. Participants will be aware of the group they have been randomly allocated to but will remain unaware of the study’s objectives. The provisional or general psychologists will not be blinded to the treatment conditions, as they will need to adhere to either the support or the therapist role.

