## Results

Recruitment began in November 2020 and was completed at the end of March 2022. In total, 240 individuals registered for the clinical trial, of which 113 (47.1%) were assessed as eligible to commence the dMH intervention. At week 3, of the 113 participants, 73 (64.6%) met the stepped care criteria to have the dMH intervention augmented with therapist assistance, whereas 40 (35.4%) remained in the program-only condition. The results of the clinical trial are forthcoming as they have recently been accepted for publication in JMIR Publications [27].

Data will be entered, screened, and analyzed using statistical software. Intention-to-treat analysis will be used for primary outcomes, controlling for baseline differences where appropriate. The primary analysis will be conducted using 2 planned contrasts comparing a change in anxiety (GAD-7) and depression (PHQ-9) scores from preintervention assessment with those of the postintervention (week 9) and follow-up (week 21) assessments, using a mixed model repeated-measure analysis. A mixed model repeated-measure analysis is preferred owing to its ability to include participants with missing data. The study will also investigate whether reliable and clinically significant change has been achieved for participants following the recommendations of Jacobson and Traux [28]. Moderation analyses will be used to determine the role of self-efficacy and motivation in engagement and adherence and their effects on anxiety and depression outcomes in the 3 treatment conditions, and a *t* test will be used to determine the impact of preferences and treatment allocations on attrition rates.

Data obtained from open-ended questions about intervention satisfaction questionnaires and from interview questions will be transcribed verbatim from audio recordings into text and then analyzed using protocols of thematic analysis to identify common themes. Text transcripts will be read several times to identify emerging themes. Thematic analysis allows for the identification of themes that are driven by the data, using an experiential, bottom-up approach [29]. Close analysis of the data will suggest names for the themes, which are likely to represent something of meaning to participants and therapists, with direct quotes used to further illustrate meaning. Researchers will meet throughout the analysis process to review and discuss the data.

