## Discussion

### Principal Findings

This study protocol presents an outline of the first adaptive intervention trial designed to determine the efficacy of various support intensities (ie, none, low, and high) of a dMH treatment program for anxiety and depression. The primary objective is to compare the efficacy of clinical outcomes (anxiety and depression) among the 3 treatment conditions. Specifically, it is predicted that therapist assistance delivered via video chat will be more effective in reducing anxiety and depression symptoms compared with program-only support. If this hypothesis is supported by the study findings, it will demonstrate that augmenting a dMH intervention with therapist assistance offered via video chat is beneficial for enhancing mental health outcomes within a community mental health treatment setting. The difference between low and high therapist assistance will also be evaluated. If the results indicate that the outcomes of these treatment conditions are similar, support will be provided for the implementation of low-intensity dMH interventions within the community, thus increasing timely community access to evidence-based interventions.

The study also has several secondary objectives that will be assessed. Examination of the role of motivation; self-efficacy; and participant preferences in engagement, adherence, and clinical outcomes among the 3 treatment conditions will be beneficial in improving our understanding of factors affecting participant attrition and engagement within dMH interventions. Qualitative evaluation of participant and therapist experiences and satisfaction with video chat technology is expected to provide further knowledge about the use of video chat for the assessment and treatment of anxiety and depression, specifically, the development of therapeutic relationships, implementation barriers and facilitators, and strengths and limitations of video chat technology. Furthermore, qualitative exploration of therapist training and implementation experiences in the delivery of dMH interventions is likely to improve the future adoption of dMH interventions incorporating video chat technology.

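### Therapist-assisted versus program-only is the stated primary comparison but is not randomised; only low versus high intensity can support a causal conclusion

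*Protocol article*

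**What the plan says.** All references are to the protocol article.

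- **Objective and hypothesis.** The first item under Objectives compares three conditions, "with particular focus on whether therapist-assisted support produces greater reductions in anxiety and depression severity" than the program alone. The Abstract's Objective says the same. Principal Findings states the hypothesis: "it is predicted that therapist assistance delivered via video chat will be more effective in reducing anxiety and depression symptoms compared with program-only support". It adds that support for the hypothesis would establish augmentation with a therapist as beneficial.
- **Randomisation.** Under Randomization: "A block randomization design will be used to randomly allocate each participant to either the low-intensity or high-intensity therapist assistance condition". On timing: "Random allocation will occur when a participant has met the criteria to be" stepped up.
- **Who stays on the program alone.** Under Life Flex Program–Only Condition: "Participants who improve or engage with the Life Flex program (program only) within the first 3 weeks maintain their no therapist assistance program".
- **The step-up rule.** Trial Design lists participants who "have symptoms of anxiety or depression that have deteriorated by >5 points", those who "show symptom improvement, but their scores remain in a severe range", those who have not read the early modules, and those without a week-3 questionnaire. Life Flex Program–Only Condition words the symptom part as no change, or scores still severe.
- **Analysis.** Under Results: "Intention-to-treat analysis will be used for primary outcomes, controlling for baseline differences where appropriate". Two planned contrasts of change from week 0 to weeks 9 and 21 are announced, in a mixed model for repeated measures. The groups being contrasted are not named.
- **Realised split.** Of 113 starters, 73 (64.6%) were stepped up and 40 (35.4%) stayed on the program alone.

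**The concern.** The comparison on which the main claim rests is between people who triggered a rule and people who did not. The rule uses early symptom course, engagement and questionnaire completion. All are measured after baseline, and all plausibly predict the week-9 score whether or not a therapist is added. A difference at week 9 or 21 then mixes any therapist effect with early response, engagement and regression to the mean. At stake is the trial's main conclusion. Limitations discusses attrition, recruitment and engagement but does not mention the non-random comparator.

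**Working it through.** **1. Allocation.** Set side by side, Trial Design, Life Flex Program–Only Condition and Randomization give this sequence: all start on the program; the rule is applied at day 15/week 3; those who trigger it are randomised to low or high; the rest continue. Nobody who triggers the rule is randomised to stay on the program alone, and nobody who does not trigger it gets a therapist. There is therefore no overlap between the groups on which an adjustment could rest.

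**2. The two versions of the rule.** An engaged participant with unchanged, non-severe scores is stepped up under Life Flex Program–Only Condition but not under Trial Design. The former section also conflicts with itself: someone who engages without improving meets both its step-up sentence and its stay sentence. These passages must be reconciled. Under any reading, assignment depends on week-3 data.

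**3. The planned analysis.** Intention-to-treat protects a randomised contrast, and this is not one. Week-0 adjustment cannot remove selection on week-3 variables. Change measured from week 0 also includes the change over weeks 0 to 3, which helped decide the group while nobody had a therapist.

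**4. What the sample size is for.** The stated 98 reproduces as a group-by-time MANOVA test with 3 groups and 3 time points (weeks 0, 9 and 21; both are assumptions): s = 2, df1 = 2 × 2 = 4, df2 = 2 × (98 − 3 − 2 + 2) = 190, λ = 98 × 2 × 0.25² = 12.25, power 0.80. Then 98 × 1.4 = 137.2, the stated 137. On this reading the sizing treats all three conditions as groups, including the non-randomised one.

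**5. Size of the selection effect if therapists do nothing.** The documents give no means, SDs or correlations, so all inputs here are assumptions. Positive values mean the therapist group looks worse.

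*A case that can be checked by hand.* Suppose the worst 64.6% on the week-3 score are stepped up, the SD is 5, and every between-visit correlation is 0.65. Here p = 0.646, p(1 − p) = 0.2287, and the normal density at the cut is φ = 0.372. Subscripts are weeks.
- Week-0-adjusted difference = SD × φ(ρ39 − ρ03ρ09) / [p(1 − p) − φ²ρ03²] = 5 × 0.372 × (0.65 − 0.4225) / (0.2287 − 0.1384 × 0.4225) = 5 × 0.0846 / 0.1702 ≈ 2.5 points.
- Raw-change difference = SD × [φ / (p(1 − p))] × (ρ39 − ρ03) = 5 × 1.63 × 0 = 0. Its sign is that of ρ39 − ρ03. If correlation decays with time, so that the 6-week correlation is below the 3-week one, it turns negative and falsely favours therapists.

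*Simulations of both written rules.* Assumptions: GAD-7 mean 11, SD 5; PHQ-9 mean 13, SD 5.5; between-visit correlation 0.5 to 0.7; 20 to 50% non-engagement; severe taken as GAD-7 ≥15 or PHQ-9 ≥20; N = 113.

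| Assumption on non-engagers | Week-0-adjusted difference, week 9 | Nominal 5% test rejects |
|---|---|---|
| Improve as much as others | 0.4 to 1.5 points | 8 to 67% of trials |
| Improve 2 points less | 1.9 to 2.5 points | 65 to 95% of trials |

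A further run of both rules gave about 0.7 to 2.6 points after adjustment. Raw change under the Trial Design rule ran from about −0.9, with correlation decaying over time, to +2.2. A simpler rule that steps up the worst 64.6% on week-3 change gave larger adjusted values, 2.2 to 4.1 points.

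**6. The contrast that is randomised.** Low versus high has 73 participants, 36.5 per arm if equal. At an assumed d of 0.5 (normal approximation), 0.5 × √(36.5/2) = 2.136 and Φ(2.136 − 1.960) = 0.57. After 30% attrition, 73 × 0.7 = 51.1, 0.5 × √(25.55/2) = 1.787 and Φ(1.787 − 1.960) = 0.43.

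**The case against.** Stepped care is a legitimate design and low versus high is properly randomised. That is correct, and it means the trial does contain a valid causal comparison. It does not help therapist versus none.

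A reader might infer that the analysis section itself names therapist versus program-only as the primary intention-to-treat contrast. It does not: the groups in the two contrasts are unnamed, and intention-to-treat is attached to the primary outcomes. The headline status rests on the Abstract, Objectives and Principal Findings.

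A reader might also infer that non-improvers always go to therapists and improvers always stay. That fits one version of the rule, not the one in Trial Design.

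The simulated sizes are open to challenge. They rest on outside assumptions, and the rejection range is wide. They were not matched to the observed split: in one re-run the Trial Design rule stepped up about 30 to 39% with 20% non-engagement and 56 to 62% with 50%, against 64.6% observed. This stands, so the figures are illustrations only.

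Finally, if the bias ran only against therapists, a favourable result would be conservative. The adjusted figures do run that way, but raw change can go the other way, and the plan adjusts only where appropriate. That reassurance is not available.

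**Conclusion.** The point holds and needs correcting before any efficacy claim is made. Therapist-assisted versus program-only is not randomised, and neither intention-to-treat nor baseline control makes it so. This follows from the allocation text alone and needs no simulation. The causal reading of a favourable result in Principal Findings is unsupported, and a null or adverse result would not show lack of benefit.

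On the stated assumptions and the two written rules, the spurious week-0-adjusted difference is roughly 0.4 to 2.6 GAD-7 points against therapists. The size depends on the rule, the correlations and the course of non-engagers; for raw change so does the direction. It would go too far to treat these figures as the bias in this trial, or to say that the trial has no valid comparison.

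**What to change.** - In the Abstract's Objective, Objectives, the analysis text under Results, and Principal Findings, state that low versus high intensity, as randomised, is the only comparison supporting a causal, intention-to-treat conclusion. Name the groups in the two planned contrasts.
- Report program-only as a non-randomised cohort: change over time with confidence intervals. Label any comparison with the therapist arms as observational, with no efficacy claim.
- Replace the sentence in Principal Findings that draws a causal conclusion from a favourable result, and add the non-random comparator to Limitations.
- Reconcile the step-up rule between Trial Design and Life Flex Program–Only Condition, and say which version was applied.

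**Cost.** This is rewording, with no new data, but it is not free. Data collection ended in March 2022 and the results were already accepted for publication, so the change of main comparison must be labelled as made afterwards and not presented as pre-specified. The 98/137 does not size low versus high: with 73 participants, power is about 57% at an assumed d of 0.5, or about 43% after 30% attrition. That should be disclosed, and a non-significant low-versus-high result should not be read as equivalence. The trial also gives up its claim to answer therapist versus none, which this design cannot answer.
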